#### Prior elicitation, informative and non-informative priors

The strength of Bayesian analyses is that it provides an algorithm for updating the probability estimate of a particular claim being true (e.g., the claim that mexiletine produces, on average, an improvement of at least 0.75 on the IVR stiffness scale in patients with NDM, when compared to placebo) whenever novel relevant evidence becomes available. The information that was already available before the novel evidence became available is expressed as prior distributions (so called “priors”). For all model parameters a prior will be needed, however, since the mean treatment difference is the parameter of main interest, these priors will receive the most attention. In the main analysis an informative prior based on data on the treatment effect from the previous study (i.e. treatment effect in the RCT by Statland et al. [13]) will be used. In a sensitivity analysis we will use a prior for the treatment effect based on expert opinion, in which case they are elicited from expert physicians: expert neuromuscular neurologists with experience in the pharmacological treatment of NDM patients. These neurologists will be asked to estimate the treatment effect based on patient demographic information, genetic information and video-clips of the baseline myotonia bedside tests. A histogram-based method (Spiegelhalter ([46], p.145) will be used to elicit individual (i.e. from each neurologist) clinical priors, which will subsequently be aggregated to provide one group clinical prior. Another sensitivity-analysis will be performed with a non-informative prior for the group level mean treatment effect instead of the informative priors. For all other model parameters we will use non-informative (or ‘flat’) priors, since it is difficult to elicit parameters such as random effect variations from physicians [46].

#### Individual interim analyses

After treatment sets 1, 2 and 3 of each N-of-1 trial we will investigate whether the existing evidence at that moment is sufficient to conclude that one of the two treatments is more effective for that particular individual. This will be done by a statistician who is blinded for treatment allocation and who will use Bayesian methods. The patient and the treating physician will be advised to discontinue the N-of-1 trial if the posterior probability of a treatment effect larger than 0.75 (clinically relevant mean difference) is at least 80% (discontinue trial participation and start regular treatment) or at most 20% (discontinue trial participation and do not start regular treatment). In all other cases they will be advised to continue the N-of-1 trial. Taking into account this advice, the physician and patient will discuss the effects of treatment, as observed by the physician and experienced by the patient, and together they will decide whether or not to continue the N-of-1 trial.

For our interim analysis we will use non-informative priors only, as we prefer to base our stopping advice on the patient data.

#### Bayesian hierarchical analysis

This study aims to answer the following questions: What is the probability that mexiletine is clinically effective in patients with non-dystrophic myotonia (NDM) on the individual and group level? To combine the results of the multiple N-of-1 trials, a hierarchical (multi-level) Bayesian model will be used, with the IVR measure for stiffness as the dependent variable, and with the patient and the subgroup (chloride versus sodium channel mutation carriers) as the structural grouping factors (or the levels of the model). The patient will be treated as a random effect (both a random intercept and a random slope), while subgroup of patients and mutation type will be treated as fixed effects. The within person residual variance will similarly be assumed to be drawn from a common distribution. In the main analysis, the prior will be based on the RCT results from Statland et al [13]. Sensitivity analyses with a clinical prior and with a non-informative prior will also be performed. From the Bayesian analysis we will obtain posterior distributions for the mean treatment effect at the population level, as well as posterior distributions for the treatment effects at the individual level, that will exhibit borrowed strength from the population estimates through shrinkage to the population mean. For details of the procedure to be used, see Zucker et al. [22].

Also, we will investigate interactions between treatment effect and treatment set, and between treatment effect and treatment order. Secondary endpoints will be analyzed similarly.

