### Combined N-of-1 trials using a Bayesian approach

In an N-of-1 trial, multiple pairs of active treatment and placebo are offered to an individual patient in a randomized, double-blind fashion, while regularly measuring key endpoints, until efficacy is established or disproved [7].

Due to their design, in which each treatment-pair should be exchangeable in time, N-of-1 trials are especially suitable for the investigation of treatments in chronic, symptomatic conditions, where period effects (i.e. changes in disease state) and carry over effects (i.e. lingering drug effect) are small. This is the case for a number of neurological, reumatological, psychiatric and pulmonary disorders [14]. N-of-1 trials are hardly applicable to surgical, quickly progressive or acute medical conditions [15]. The method has been originally developed to identify the best treatment option for an individual patient in case of genuine doubt concerning treatment benefit by formalization of what a physician does on a daily basis [14,16].

Major advantages of N-of-1 trials from the point of view of the patient and the treating physician are: (1) an N-of-1 trial determines whether the treatment is actually of benefit in the individual patient as opposed to some percentage of a group of patients; (2) the N-of-1 trial avoids the possibly unethical “therapeutic misconception” of the RCT - where most subjects are convinced they are receiving effective treatment even though told there is a 50/50 chance they will receive placebo (and that the treatment may not be effective) [16-19].

More recently, data from multiple N-of-1 trials have been combined (or meta-analyzed) to produce estimates of treatment effect at a population level (i.e. combined N-of-1 trials) [20-22]. For this purpose, Bayesian hierarchical models have been developed [23,24]. Bayesian models use a different approach, which does not rely on the hypothesis testing/confidence intervals paradigm of traditional (frequentist) statistical methods, but allows determination of the posterior probability of whether a treatment effect is beneficial. Additionally, Bayesian methods allow for the use of prior available information (e.g. previous trial results) within the analysis [7].

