## Methods/Design

### Design

In this study a series of double-blind, randomized and placebo-controlled N-of-1- trials is conducted. Each individual N-of-1 trial consists of one to four treatment sets, each comprising 11 weeks. A treatment set comprises two treatment periods: a four-week period of active treatment (mexiletine) and a four-week period of treatment with placebo, with a one-week wash-out in between treatment periods and two weeks for statistical analysis (individual interim analysis) at the end of each treatment set. Within each treatment set, the order in which mexiletine and placebo will be offered will be randomized (block-randomization). Total study duration will be between 11 and 44 weeks per patient, depending on the amount of treatment sets needed to produce convincing evidence of clinical effectiveness or ineffectiveness of mexiletine (Figure 1). Results of the individual N-of-1 trials will be combined to produce estimates of population clinical and cost-effectiveness by using a hierarchical Bayesian model [25]. The trial is performed at the Radboud University Medical Center in Nijmegen, The Netherlands.

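### The primary model names no period term, and the planned treatment-by-order interaction is the period effect under another name

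*Protocol article*

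**What the plan says.** Under Design, "A treatment set comprises two treatment periods: a four-week period of active treatment (mexiletine) and a four-week period of treatment with placebo". The two periods are separated by a wash-out of one week. The same section states that "Within each treatment set, the order in which mexiletine and placebo will be offered will be randomized". Order is therefore a property of each set, and a patient may have one to four sets.

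Under Bayesian hierarchical analysis, the patient has random effects for intercept and slope, "while subgroup of patients and mutation type will be treated as fixed effects". Period is not listed. The section then adds that "we will investigate interactions between treatment effect and treatment set, and between treatment effect and treatment order", says that secondary endpoints are handled in the same way, and refers to a cited methods paper for details.

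The Background says that N-of-1 designs suit conditions "where period effects (i.e. changes in disease state) and carry over effects (i.e. lingering drug effect) are small". The Hypothesis section calls the disease stable and says that the drug effect subsides quickly. No size for a period effect is given anywhere.

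**The concern.** In a two-period set, whether a score comes from the first or the second period is fixed once treatment and order are known. The check listed as an interaction is therefore the period main effect. Two things follow.

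- A simple drift in scores from first to second period, with the drug working equally well in both orders, would surface as a treatment-by-order interaction. Under that label it invites the conclusion that mexiletine works differently depending on order.
- The stated model that produces the treatment effects does not remove the drift. The study asks about effectiveness at both individual and group level, and the individual estimates have the least averaging to protect them.

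**Working it through.** The plan gives no figure for a period effect, so there is none to reproduce. Its expected posterior probability of 0.82 does not bear on this point.

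**Inputs from the protocol article.** Within-subject SD 1.5 and clinically relevant difference 0.75 (Sample size and power); 30 patients; daily scores over the last two weeks of each period, taken as 14 independent scores; the interim thresholds of 80% and 20% with a non-informative prior (Individual interim analyses).

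**Assumed, because the documents give no value.** Period shift D of 0, 0.25 or 0.5; between-patient slope SD of 0.5 or 0.89; mean effect of 0.75 to 1.75.

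**1. The identity.** Code treatment T = +1 for mexiletine and −1 for placebo; order O = +1 for mexiletine first and −1 for placebo first; period P = +1 for first and −1 for second.

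| Cell | T | O | T×O | P |
|---|---|---|---|---|
| Mexiletine first, period 1 | +1 | +1 | +1 | +1 |
| Mexiletine first, period 2 | −1 | +1 | −1 | −1 |
| Placebo first, period 1 | −1 | −1 | +1 | +1 |
| Placebo first, period 2 | +1 | −1 | −1 | −1 |

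The last two columns agree in every cell. With τ the treatment contrast and D the first-minus-second shift, the expected difference is τ + D with mexiletine first and τ − D with placebo first. The gap between orders is (τ + D) − (τ − D) = 2D. A shift of 0.75 with no effect modification would show as a gap of 1.5, twice the clinically relevant difference.

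**2. How much stays in a patient's raw estimate.** With orders drawn independently per set, the share of patients by remaining fraction of D is:

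- 1 set: full D in 100%.
- 2 sets: full in 50%, zero in 50%.
- 3 sets: full in 25%, one third in 75%.
- 4 sets: full in 12.5%, half in 50%, zero in 37.5%.

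**3. How many patients have one set, if the interim advice is followed.** The standard error of one set's difference is 1.5 × √(2/14) = 0.567. Stopping needs a distance from 0.75 of at least h = 0.8416 × 0.567 = 0.477. With S = √(slope SD² + 0.567²) and δ = mean effect − 0.75 ± D, the stopping probability is Φ((δ − h)/S) + Φ((−h − δ)/S), averaged over the two orders.

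- Mean 0.75, slope SD 0.5, D = 0.5: S = 0.756, giving Φ(0.03) + Φ(−1.29) = 0.512 + 0.098 = 0.61. The other order gives the same value by symmetry.
- Mean 1.75, slope SD 0.89, D = 0.5: about 0.78.

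This gives about 60–80%. Without a shift the range is about 53–78%, falling to 50% at the low end with 10 scores per period, the number used in the sample-size simulation.

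**4. Group level.** The expected bias over randomisation is about zero. The chance bias has SD D/√30 = 0.18D with one set each and D/√60 = 0.13D with two. An estimated slope variance takes up the shift: with two sets each, slope SD 0.5 and D = 0.5, the apparent slope SD becomes √(0.5² + 0.5²/2) = 0.61. Simulation with estimated slope variance (30 patients, the interim rule, mean effect 1.75, slope SD 0.5, D = 0.5) gave a true SD of 0.159 against a model SE of 0.149 without the term, and 0.140 against 0.131 with it. The ratios, 0.149/0.159 and 0.131/0.140, are both 0.94.

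**5. Individual level, same simulation.**

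- D = 0.5: RMSE 0.47 without the term against 0.38 with it (slope SD 0.5), and 0.59 against 0.48 (slope SD 0.89).
- D = 0.25, slope SD 0.5: 0.383 against 0.371 in a run with known variances, a small gain.
- D = 0: the term adds about 0.002–0.003 to the group SE and about 0.005–0.02 to the individual RMSE.

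**The case against.** The strongest reply is that this is a condensed article. Its list of fixed effects is plainly incomplete, since it does not name treatment itself. It defers to a cited methods paper, and its frequentist comparison follows the earlier cross-over trial; neither source is shown, and either may carry a period term. Nuisance terms are commonly left to the analysis plan. The article also presumes small period effects in a stable disease, and fitting the interaction with suitable coding is itself a period adjustment, so the check is already planned. Much of this stands and limits the weight of the point. It does not remove it, because the article itself puts order in the role of an effect modifier to be investigated.

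Some stronger readings are tempting, but the documents do not support them.

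- *The shift is left in every patient's estimate.* It is not: it cancels or is diluted in many patients with two or more sets (step 2).
- *The group standard error is materially understated.* Holding the variances known gives a true SD of 0.152 against a model SE of 0.131, which suggests a 14% shortfall. The planned model estimates the slope variance, and the shortfall is then about 6% with or without the term.
- *Most patients will stop after one set.* That depends on assumed effects. The interim result is only advice, and the sample-size simulation assumes two sets for everyone.
- *The plan will report effect modification.* It says only that the interaction will be investigated. Misreading is a risk of the label and is not stated as a planned conclusion.

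**Conclusion.** The point holds as a cheap improvement. As described, the primary model has no period term, and the treatment-by-order interaction is exactly the period effect, taking order to mean the order within a set. Naming that contrast the period effect also presumes negligible carry-over, as the protocol does.

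The consequence is mainly for individual estimates: about a fifth in RMSE at an assumed D of 0.5 (0.09/0.47 and 0.11/0.59 are both about 19%), and little at 0.25. The group mean stays about unbiased and its standard error broadly honest, with some precision lost. The size rests on D, the slope SD and the mean effect, none of which the documents give. If period effects are as small as the protocol presumes, little changes numerically and the gain is mostly in correct labelling.

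**What to change.** Add a fixed term for period within set (first or second) to the primary hierarchical model and to the secondary-endpoint models. Report the treatment-by-order contrast as the period effect, not as an interaction. If the full analysis plan already has such a term, only the wording in the article needs to be aligned with it.

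The cost is one extra parameter and the small loss at D = 0 shown in step 5. The term does not repair a patient-only interim analysis after the first set: with one period per treatment, period and treatment cannot be separated within that patient, and only pooling across patients can do so.

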#### Comparisons with the RCT and traditional analysis methods

In addition to synthesizing the data from our study with the existing RCT evidence, we will also contrast the outcomes of the two studies. To this end, a sensitivity analysis with a non-informative prior will be performed. This will provide a direct comparison of the outcomes of the two studies. In order to compare the novel methodology of combined N-of-1 trials with more traditional analysis methods, we will perform a (non-Bayesian) frequentist analysis of our data, where the same approach will be chosen as in the previous cross-over RCT by Statland et al. [13].

## Discussion

In conclusion, our study offers a unique opportunity to assess the validity and feasibility of Bayesian analyses of combined N-of-1 trial methodology to obtain evidence of the clinical and cost-effectiveness of drugs for rare diseases, at the individual and group level simultaneously.

Furthermore, our approach, if valid and feasible, may reduce costs compared to an international RCT, and enables clinicians to potentially run trials in the setting of out-patient clinic visits.

As such, our study may serve as a model for future research into treatments in other rare genetic diseases, and will help to bridge the gap between research and clinical practice.

Apart from this methodological objective, results of our study will contribute to the current level of evidence of the clinical-effectiveness of mexiletine in NDM and may clarify the cost-effectiveness of mexiletine treatment in NDM patients.

## Abbreviations

NDM: Non-dystrophic myotonia
NDMs: Non-dystrophic myotonic syndromes
CINCH: Consortium of clinical investigation of neurological Channelopathies
CVZ: National health insurance board of The Netherlands
RCT: Randomized controlled trial
EMA: European medical agency
FDA: Food and drug administration
EU: European union
CLCN1: Skeletal muscle chloride channel gene
SCN4A: Skeletal muscle sodium channel gene
PO: Per Os
BMC: Becker myotonia congenita
TMC: Thomsen myotonia congenita
PMC: Paramyotonia congenita
SCM: Sodium channel myotonia
IVR: Interactive voice response system
EMG: Electromyogram
ECG: Electrocardiogram
INQoL: The Individual neuromuscular quality of life questionnaire
SF-36: The Short-form 36-item health status survey
TUG: The Timed up & go
MVIC: Maximal voluntary isometric contraction
PF: Peak force
ICER: The incremental cost-effectiveness ratio
CSRI: The client service receipt inventory
CRCN: Clinical research centre nijmegen
DSMB: Data and safety monitoring board
ZonMw: The Netherlands organisation for health research and development
QoL: Quality of life
GP: General practitioner
MCID: Minimal clinically important difference
